**Definitions of Dose Limiting Toxicity (DLT)**

Newly appeared ≥ grade 3 adverse event that is related to UC-MSCs infusion occurred from the start of UC-MSC infusion to 1 month after the last infusion, and cannot be relieved to grade 1 within 72 hours after treatment with drugs or other interventions.

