| **Cell product specification** | Umbilical cord-derived mesenchymal stem cells, mainly composed of human umbilical cord-derived mesenchymal stem cells in vitro, 5mL/bag, containing 2.0×10^7^ cells. The cell cryopreservation solution is a compound electrolyte solution containing 5% human serum albumin and 10% dimethyl sulfoxide (DMSO). |
| **Trial design and protocol** | Following the "3+3" dose escalation design principle, three escalating dose groups A, B, and C were established and 3 subjects were enrolled in each dose group sequentially. Groups A, B, and C received 0.5×10^6^ cells/kg, 1.0×10^6^ cells/kg and 2.0×10^6^ cells/kg respectively, intravenously infused once a week for four weeks (4 times). During the dose-escalation period, the occurrence of adverse reactions in the three groups was observed and dose-limiting toxicity (DLT) was judged. Once dose-limiting toxicity occurs, the investigator will decide to add 3 subjects to the current dose group (i) or the lower dose group (i-1, i≠ the lowest dose group) according to the number of DLT cases to continue observation or stop the trial. According to the safety data of the dose-escalation period, the researchers selected an appropriate dose expansion group (A or B or C) to enroll 6 subjects for the dose-expansion period to further observe the efficacy of UC-MSCs. |
| **operation process of cell product infusion** | Subjects should be given 5mg dexamethasone to prevent post-infusion reactions prior to infusion, and the infusion duration should generally not exceed 1 hour. During infusion, patients' vital signs and adverse reactions should be closely observed. If adverse symptoms occur, infusion speed should be slowed down or stopped as appropriate. |
| **Treatment course** | 28 days |

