# 5. Study Design and Statistical Methods

## 5.1 Study Design

This is a single-centre, open-label, single-arm study, which is divided into two-stage: dose-escalation stage, and dose-expansion stage.

In the dose-escalation stage, three successively increasing dose groups were set up, and the initial dose of the study was the lowest dose group. Subject enrollment, judgment and treatment of dose-limiting toxicity (DLT) refer to the traditional "3+3" dose-escalation design principle. That is, starting from the lowest dose group, 3 subjects were enrolled each time. If no DLT is observed, the trial will be continued at the next level dose; if DLT occurs in one of three patients, three more patients will be enrolled in the current dose, and when no DLT occurs anymore, the trial will be continued at the next level dose. If 2 or more DLTs occur in the 3 or 6 patients, the dose escalation will be stopped, and the current dose will be determined as the maximum tolerated dose (maximum tolerated dose, MTD). The flow of this trial is shown in Figure 1. Considering the safety of UC-MSCs, there will be 9 to 12 patients enrolled in the dose-escalation stage.

[figure not shown]
**Figure 1.** “3 + 3” dose-escalation protocol

[figure not shown]
The final dose in the dose-expansion phase will be determined based on the MTD in the dose-escalation phase, safety, efficacy, and opinion considered by the principal investigator, six patients will be enrolled in the dose-expansion stage to preliminarily explore the efficacy.

**Figure 2.** Six subjects will be enrolled to further evaluate the safety and efficacy of this dose infusion of umbilical cord MSCs

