# Usage, Dosage, Time and Course of Umbilical Cord-derived MSCs

## 9.1 Usage and Dosage of Umbilical Cord-derived MSCs

1. Name of cell products: Umbilical cord-derived MSCs.
2. Specification: 5mL/bag, the main component is MSCs derived from human umbilical cord cultured in vitro, containing 2.0×10^7^ cells. The cell cryopreservation solution is a compound electrolyte solution containing 5% human serum albumin and 10% dimethyl sulfoxide (DMSO).
3. Usage of cell products: Divide into 3 dose-escalation groups (Group A, Group B, and Group C) in turn, with 3 subjects in each group and proceed sequentially from low dose to high dose group according to the principle of dose-escalation. The specific number of subjects in the group is based on a traditional "3+3" dose-escalation protocol, 3 subjects will be enrolled each time, and if no DLT occurs in 3 cases, the trial will be continued at the next level dose; if DLT occurs in 1 of 3 patients, 3 more patients will be enrolled in the current dose, and when no DLT occurs anymore, the trial will be continued at the next level dose. If 2 or more DLTs occur in the 3 or 6 patients, the dose escalation will be stopped, and the current dose will be determined as the MTD.
4. 3 dose-escalation groups- Group A, Group B, and Group C:

- The dose of each infusion in Group A is 0.5×10^6^ cells/kg, intravenous infusion, once a week for a total of 4 times;
- The dose of each infusion in Group B is 1.0×10^6^ cells/kg, intravenous infusion, once a week for a total of 4 times;
- The dose of each infusion in Group C is 2.0×10^6^ cells/kg, intravenous infusion, once a week for a total of 4 times;

According to the above test results, the investigator will determine a specific dose experimental group (one of Group A, B, or C), and expand the sample size of the subjects to 6 cases.

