# Management of Infusion Reactions

## 10.1 Delay/Pause/Stop Administration

If subjects experience any of the following adverse events, it is recommended to suspend or discontinue the administration of UC-MSCs to allow the subjects to recover from the toxicity, whether the adverse events are related to the administration or not.

- Criteria for discontinuation of administration are as follows:

1. If severe allergy occurs during the infusion process, such as anaphylactic shock, the administration should be stopped immediately and patients should be withdrawn from the trial;
2. If arterial or venous thrombosis occurs during the infusion process, such as deep vein thrombosis, myocardial infarction, etc., the investigator needs to judge the correlation with the infusion of UC-MSCs, and determines whether to continue the administration;

- Criteria for delay of administration are as follows:

1. Severe bleeding symptoms, such as gastrointestinal hemorrhage, and cerebral hemorrhage;
2. Febrile or infectious neutropenia;
3. Grade 3 or higher non-hematological toxicity, except in the following cases:

- Grade 3 nausea that can resolve with antiemetic treatment within 7 days
- Grade 3 vomiting that can resolve with antiemetic treatment within 7 days
- Grade 3 diarrhea that can resolve with antidiarrheal treatment within 7 days
- Grade 3 fatigue
- Grade 3 Weakness

If any of the above adverse effects occur, it is recommended to pause umbilical cord-derived MSC dosing until recovery to ≤ Grade 2 or baseline; Dosing should be restarted according to treatment schedule (Grade 2 laryngeal edema or Grade 2 bronchospasm requires full recovery).

In addition, if the platelet counts are ≥300×10^9^/L during the infusion, the drug administration can be suspended until the platelet counts are less than 300×10^9^/L, and then the administration can be resumed.

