**Infusion-related reaction*****CTCAE Term**

| **Grade** | **CTCAE Term** |
| --- | --- |
| 1 | Mild transient reaction; infusion interruption not indicated; intervention not indicated |
| 2 | Therapy or infusion interruption indicated but responds promptly to symptomatic treatment (e.g., antihistamines, NSAIDs, narcotics, IV fluids); prophylactic medications indicated for ≤24 hrs |
| 3 | Prolonged (e.g. not rapidly responsive to symptomatic medication and/or brief interruption of infusion); recurrence of symptoms following initial improvement; hospitalization indicated for clinical sequelae |
| 4 | Life-threatening consequences; urgent intervention indicated |
| 5 | Death |

Definition: A disorder characterized by an adverse reaction to the infusion of pharmacological or biological substances.

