### 10.2.2 Grade 3 Infusion-related Reactions

If subjects experience a Grade 3 infusion-related reactions:

- - - The infusion should be stopped immediately.
    - Subjects should receive appropriate treatment with H1 receptor antagonists and/or paracetamol or prednisolone as clinically needed, with additional drugs added such as epinephrine and bronchodilators if needed.
    - Once symptoms are relieved, the infusion can be continued at an infusion rate not exceeding 50% of the initial rate until complete dosing. If Grade 3 symptoms recur, repeat the above steps. When the Grade 3 infusion-related reactions occur for the third time, subjects should terminate the infusion and should not receive further study drug treatment.

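### Anaphylaxis, grade 4 reactions and other dosing-ending reactions do not count as DLTs if they settle to grade 1 within 72 hours, so a cohort can score 0/3 and the dose doubles

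*Protocol*

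**What the plan says.** The DLT definition following section 5.1 joins two conditions. The event must be new, related to the infusion, of grade 3 or higher and inside a window that closes one month after the last infusion. It must also be one that persists: "and cannot be relieved to grade 1 within 72 hours after treatment with drugs or other interventions". No event type or grade is exempt from the second condition.

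Escalation depends on that count. Section 5.1: "If no DLT is observed, the trial will be continued at the next level dose". Section 9.1 repeats it: "if no DLT occurs in 3 cases, the trial will be continued at the next level dose". In the synopsis, adding patients or stopping is likewise triggered by a DLT: "Once dose-limiting toxicity occurs, the investigator will decide to add 3 subjects to the current dose group (i) or the lower dose group". The three levels are 0.5, 1.0 and 2.0 × 10^6 cells/kg.

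For the individual patient the protocol is stricter:

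- Section 10.1, severe allergy: "such as anaphylactic shock, the administration should be stopped immediately and patients should be withdrawn from the trial".
- Section 10.2 grades an infusion reaction as grade 4 when it has "Life-threatening consequences; urgent intervention indicated", and section 10.2.3 then ends study treatment.
- Section 10.2.2: "When the Grade 3 infusion-related reactions occur for the third time, subjects should terminate the infusion and should not receive further study drug treatment".

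**The concern.** A reaction can be serious enough that the protocol bars the patient from further cells, yet add nothing to the tally that decides whether the next three patients receive double the dose.

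The 72-hour relief condition suits toxicities that build and linger. It suits acute infusion reactions poorly, because these may be treated and over quickly however dangerous they were. The protocol foresees such reactions: it premedicates every patient with dexamethasone and sets out management by grade. For grade 3 reactions it plans relief and then resumption of the same infusion: "Once symptoms are relieved, the infusion can be continued at an infusion rate not exceeding 50% of the initial rate until complete dosing". Relief well inside 72 hours is therefore an expected course for grade 3.

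Safety is the primary endpoint, and the MTD from escalation feeds the choice of expansion dose. A DLT count that misses this class of event weakens both.

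**Working it through.** **1. Reading the clauses together**

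| Event (related, new, in window) | Effect on the patient | DLT if at grade 1 within 72 h? |
|---|---|---|
| Anaphylactic shock | Stopped and withdrawn (10.1) | No |
| Grade 4 infusion reaction | No further study drug (10.2.3) | No |
| Third grade 3 infusion reaction, each episode judged relieved | No further study drug (10.2.2) | No |
| Death | – | Not relievable, so already a DLT |

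A cohort in which one or two of three patients had such a reaction can thus be scored 0/3. The protocol does not say whether a patient withdrawn under 10.1 stays evaluable or is replaced. Neither reading adds a DLT.

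**2. The plan's own figures**

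Three levels × 3 patients = 9 in escalation, plus 6 in expansion = 15, the stated minimum. One expanded cohort gives 12, the top of the stated 9–12 range. Two give 15 and three give 18.

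**3. Size of the effect**

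The documents give neither a reaction rate nor the share relieved in time, so both are assumptions:

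- r = per-patient rate of the reactions at issue: 5%, 10%, 20% or 33%.
- Half are relieved to grade 1 within 72 hours, so the counted rate falls from p = r to p = r/2.
- Other grade 3 events are handled the same either way and are left out.

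With q = 1 − p:

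- Clear a level: q³ + 3pq² × q³
- Score 0/3 although at least one patient had an uncounted reaction: (1 − r/2)³ − (1 − r)³
- Reach the top dose, same rate at each level: (clear a level)²

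Worked for r = 20%:

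- All counted: 0.8³ + 3 × 0.2 × 0.8² × 0.8³ = 0.512 + 0.384 × 0.512 = 0.709.
- Half uncounted: 0.9³ + 3 × 0.1 × 0.9² × 0.9³ = 0.729 + 0.243 × 0.729 = 0.906.
- Missed cohort: 0.729 − 0.512 = 0.217.
- Top dose: 0.709² = 0.50 against 0.906² = 0.82.

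| r | Clear a level: all counted vs half uncounted | 0/3 despite a reaction | Reach top dose: all counted vs half uncounted |
|---|---|---|---|
| 5% | 0.973 vs 0.993 | 0.069 | 0.948 vs 0.986 |
| 10% | 0.906 vs 0.973 | 0.128 | 0.821 vs 0.948 |
| 20% | 0.709 vs 0.906 | 0.217 | 0.502 vs 0.821 |
| 33% | 0.434 vs 0.783 | 0.281 | 0.189 vs 0.613 |

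If every such reaction counted, the third column would be zero.

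The result is sensitive to the share relieved. With 80% relieved, the chance of clearing a level at r = 20% is 0.983 and at r = 33% it is 0.956. With all relieved it is 1 at any rate.

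**The case against.** The strongest reply is that this is a deliberate and internally consistent choice. Ending one patient's treatment and declaring a dose level intolerable are different decisions, and nothing in the protocol shows that acute reactions depend on cell dose. Requiring relief to grade 1 is also tighter than the dosing rule in 10.1, which resumes at grade 2 or baseline. All of that is fair for ordinary grade 3 events. It does not explain why a life-threatening related event should be invisible to the escalation rule.

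There are real safeguards. Section 13.4 directs suspension for a serious safety problem, 15.1 makes life-threatening events reportable, 15.2 requires immediate protective measures and reporting of serious adverse events, and 13.5 lets the regulator intervene. The expansion dose rests on safety data and the investigator's opinion as well as the MTD. An extreme cluster would probably be caught, and an uncounted reaction can still bear on the expansion dose. But none of these clauses sets an escalation threshold or alters the count, so one or two patients in a cohort remain the gap.

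The rates are assumed, and 20–33% may be high for so narrow a class of event. The protocol expects low immunogenicity and no obvious adverse events. At 2% the chance of clearing a level is 99.5% against 99.9%. The model also ignores any suspension under 13.4, so its differences are upper bounds on that score. These points limit the size of the effect but leave the reading of the text intact.

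The third grade 3 reaction is the weakest case. Grade 3 covers prolonged or recurring reactions, and an investigator could call one that returns on each rechallenge unrelieved and score a DLT.

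**Conclusion.** The concern holds. As written, a related anaphylactic shock, grade 4 reaction or other dosing-ending reaction that settles to grade 1 within 72 hours is not a DLT, and a cohort containing one can score 0/3 and trigger a doubling of dose. That conclusion comes from the text and needs no assumed rate.

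The practical size does depend on assumptions: the rate of such reactions, half of them relieved in time, the same rate at every level for the top-dose figures, and no one invoking 13.4 or 15.2. On those terms the effect on clearing a level is small at a 5% rate and becomes material from about 10–20%. The gap should be closed, because it lies in the rule that governs dose doubling and is cheap to remove.

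**What to change.** Add to the DLT definition: *Any UC-MSC-related grade 4 or 5 event, any related anaphylaxis, and any related grade 3 or higher event that permanently ends dosing (including a third grade 3 infusion-related reaction) is a DLT regardless of recovery time.* Keep the 72-hour clause for all other grade 3 events. Grade 5 is named only for clarity.

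At each escalation decision, list patients permanently stopped for toxicity beside the DLT count. If escalation is already complete, re-judge the earlier cohorts against the new definition before confirming the expansion dose. Recruitment was planned for June 2019 to June 2021; actual status is not shown.

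The cost is one sentence, one line in the listing and, where cohorts have been treated, a review of their events. The downside is more three-patient expansions. The chance of one at a level is 3pq², all counted against half uncounted:

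| r | Expansion at a level | More than 12 escalation patients |
|---|---|---|
| 5% | 14% vs 7% | 4% vs 1% |
| 10% | 24% vs 14% | 9% vs 4% |
| 20% | 38% vs 24% | 12% vs 9% |

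The last column enumerates all paths through the three levels. The current rule can already pass 12, so restate the 9–12 range in sections 5.1, 5.21 and 7 in the same edit.

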**5.2 Statistical Methods**

### 5.21. Sample Size Estimation

Three dose groups will be set in the dose-escalation stage, 3 subjects will be enrolled each time and 9-12 patients will be enrolled in total according to the "3+3" dose-escalation protocol.

There will be 6 patients enrolled in the dose-expansion stage to explore the efficacy.

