# 7. Number of Subjects

At least 15 patients are expected to be recruited.

Three dose groups will be set in the dose-escalation stage, 3 subjects will be enrolled each time and 9-12 patients will be enrolled in total according to the "3+3" dose-escalation protocol.

There will be 6 patients enrolled in the dose-expansion stage to explore the efficacy.

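### The 9–12 escalation patients attributed to the 3+3 rule do not follow from it (the rule gives 3 to 18), and section 9.1 words the expansion size differently from the rest of the protocol

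*Protocol*

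**What the plan says.** **Escalation size.** Section 5.21 states: "Three dose groups will be set in the dose-escalation stage, 3 subjects will be enrolled each time", and continues that "9-12 patients will be enrolled in total", in accordance with the 3+3 scheme. Section 7 repeats this. Section 5.1 gives the same range but introduces it by reference to the safety of the product.

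**The rule.** Section 5.1 (repeated in substance in section 9.1) has four parts:
- Cohorts of three: "starting from the lowest dose group, 3 subjects were enrolled each time".
- No DLT: "If no DLT is observed, the trial will be continued at the next level dose".
- One DLT in three: "if DLT occurs in one of three patients, three more patients will be enrolled in the current dose".
- Stop: "If 2 or more DLTs occur in the 3 or 6 patients, the dose escalation will be stopped".

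The synopsis adds that, after a DLT, three subjects may be added at the current or the next lower level.

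**Expansion size.** The synopsis and sections 5.1, 5.21 and 7 each have six patients enrolled in the expansion stage. Section 9.1, having set three subjects per group, says the investigator will pick one group and "expand the sample size of the subjects to 6 cases".

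**Total.** Section 7: "At least 15 patients are expected to be recruited". The synopsis gives at least 15 cases and, in its schedule, a plan for 15.

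**The concern.** Sections 5.21 and 7 present 9–12 as a consequence of the 3+3 rule, but the rule sets neither a floor of 9 nor a ceiling of 12. These are the two sections to which a reader goes for the sample size, and neither states the assumption that would justify the narrower range.

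The expansion wording is a separate problem. Bringing a group up to six and enrolling six further patients are different recruitment instructions. They lead to different totals and to different numbers at the selected dose, which is where the preliminary efficacy evidence will come from. A later analysis plan cannot settle this, because it is a conflict between enrolment instructions in the protocol itself.

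**Working it through.** **Inputs.** Three levels, cohorts of three, at most six per level, stop at two or more DLTs in 3 or 6 patients (sections 5.1, 5.21 and 9.1). The DLT rate p is not given anywhere; 1% to 20%, constant over levels, is assumed here for illustration.

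**Where the stated figures come from.** 3 × 3 = 9 is the size with no DLT. Adding one second cohort gives 9 + 3 = 12. So 9–12 describes a trial that treats all three levels and opens a second cohort at no more than one of them. The total of 15 reproduces as 9 + 6.

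**What the rule allows.**
- Minimum: two or more DLTs in the first three patients at level A, so 3.
- Maximum: a second cohort at every level, 3 × 6 = 18.
- All three levels completed: 9 to 18.
- Possible sizes: 3, 6, 9, 12, 15, 18.

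**Probabilities.** For one level:
- pass with 3: a = (1−p)³
- pass with 6: b = 3p(1−p)² × (1−p)³
- stop with 3: s = 1 − (1−p)³ − 3p(1−p)²
- stop with 6: t = 3p(1−p)² × [1 − (1−p)³]

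At p = 0.10: a = 0.729; b = 0.243 × 0.729 = 0.1771; s = 0.028; t = 0.243 × 0.271 = 0.0659.
- P(3) = s = 0.028
- P(6) = t + a·s = 0.0659 + 0.0204 = 0.0863
- P(15) = b²(a+s) + 2ab(b+t) = 0.0238 + 0.0628 = 0.0865
- P(18) = b²(b+t) = 0.0076

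Below 9: 0.028 + 0.0863 = 0.1143. Above 12: 0.0865 + 0.0076 = 0.0941. Outside 9–12: 0.2084.

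The same enumeration at the other rates (any path ending on 9 or 12 counts as inside, including those that stop early):

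| Assumed DLT rate | 9 or 12 | Below 9 | Above 12 | Outside 9–12 |
|---|---|---|---|---|
| 1% | 99.61% | 0.15% | 0.24% | 0.39% |
| 2% | 98.55% | 0.57% | 0.88% | 1.45% |
| 5% | 92.68% | 3.28% | 4.04% | 7.32% |
| 10% | 79.16% | 11.43% | 9.41% | 20.84% |
| 20% | 53.94% | 34.46% | 11.60% | 46.06% |

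If the synopsis option is applied by adding three patients at the next lower level after a stop, where that level has only three, the chance of 9 or 12 is 77.3% at a 10% rate and 53.3% at 20%. The conclusion does not depend on which version is used.

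**Expansion and total.**

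| | Six new patients | Group brought to six |
|---|---|---|
| No DLT, total | 9 + 6 = 15 | 9 + 3 = 12 |
| Selected group has 3: patients at that dose | 9 | 6 |
| Selected group already has 6: patients at that dose | 12 | 6 (none added) |

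With six new patients and all three levels completed, the total runs from 9 + 6 = 15 to 18 + 6 = 24. If the trial ends at level A with no expansion, the total is 3 or 6.

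**The case against.** The best defence is that 9–12 is a planning expectation. Section 5.1 ties it to the product's safety, section 4 expects no obvious adverse events from the infusion, and the DLT definition is narrow: new, related, grade 3 or higher, and not relieved to grade 1 within 72 hours. At a DLT rate of 1% or 2% the range would hold with probability 99.6% or about 98.5%. At 20%, most of the shortfall is early stopping (34.5 of 46.1 percentage points), which is how a 3+3 design is meant to behave. All of that stands. It supports calling 9–12 an expectation; it does not support sections 5.21 and 7, which drop the qualifier and credit the range to the rule.

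On the expansion, four places agree on six enrolled, only that reading produces 15, and section 9.1 may simply be loosely worded. That is fair, but the sentence stands in the section that directs dosing and enrolment, and it still has to agree with the others.

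Three stronger readings are tempting, and the documents do not support them:
- **That the design fails to deliver at least 15.** The no-DLT total is exactly 15 under the majority wording, every path that completes all levels and adds six new patients reaches 15 or more, and section 7 speaks of an expectation.
- **That 12 is a cap which invites skipping a required second cohort.** Nothing limits enrolment at 12 or waives that cohort; sections 5.1 and 9.1 both require it.
- **That the correct overall total is 9 to 24.** The floor of 9 would count six expansion patients after a stop at level A, where the total could be 3 or 6.

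**Conclusion.** The point holds in two limited parts. First, 9–12 is wrong as a range derived from the stated 3+3 rule, which gives 3 to 18, or 9 to 18 if all three levels are completed. How much this matters depends on a DLT rate that the protocol does not give: the chance of falling outside 9–12 is negligible at 1–2% (0.4% to 1.5%), about 7% at 5%, 21% at 10% and 46% at 20%. The chance of needing more than 12 is 0.2%, 0.9%, 4%, 9% and 12% at 1%, 2%, 5%, 10% and 20%. These figures assume a constant rate across levels and independent patients.

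Second, section 9.1 conflicts with the synopsis and sections 5.1, 5.21 and 7 on the expansion size, a difference of three patients (12 against 15) when no DLT occurs. The total of at least 15 is sound as a plan, but not as an unconditional minimum.

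**What to change.** - **Sections 5.21 and 7:** state the rule-based range, 3–18 patients (9–18 if all three levels are completed). Keep 9–12 only as an expectation, with the DLT rate assumed for it. Align the sentence in section 5.1.
- **Section 9.1:** reconcile it with the synopsis and sections 5.1, 5.21 and 7, saying explicitly whether six is the number of new patients or the final size of the chosen group, and what happens if that group already has six.
- **Synopsis and section 7:** if the six are new patients, present 15 as the planned total when all three levels are completed and those six are added (15–24 on those paths). Add that an early stop can give fewer, down to 3 or 6 if the trial ends at level A without expansion.

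These are text changes; no dose or escalation rule is altered. The cost is a less tidy stated range and a larger worst-case budget and cell supply to plan for.
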